# Shoulder function and work disability after decompression surgery for subacromial impingement syndrome: a randomised controlled trial of physiotherapy exercises and occupational medical assistance

**DOI:** 10.1186/1471-2474-15-215

**Published:** 2014-06-21

**Keywords:** Acromioplasty, Oxford Shoulder Score, Physiotherapy, Randomised controlled trial, Rehabilitation, Shoulder, Sickness absence, Surgery, Training, Work retention

## Abstract

**Background:**

Surgery for subacromial impingement syndrome is often performed in working age and postoperative physiotherapy exercises are widely used to help restore function. A recent Danish study showed that 10% of a nationwide cohort of patients retired prematurely within two years after surgery. Few studies have compared effects of different postoperative exercise programmes on shoulder function, and no studies have evaluated workplace-oriented interventions to reduce postoperative work disability. This study aims to evaluate the effectiveness of physiotherapy exercises and occupational medical assistance compared with usual care in improving shoulder function and reducing postoperative work disability after arthroscopic subacromial decompression.

**Methods/Design:**

The study is a mainly pragmatic multicentre randomised controlled trial. The trial is embedded in a cohort study of shoulder patients referred to public departments of orthopaedic surgery in Central Denmark Region. Patients aged ≥18–≤63 years, who still have shoulder symptoms 8–12 weeks after surgery, constitute the study population. Around 130 participants are allocated to: 1) physiotherapy exercises, 2) occupational medical assistance, 3) physiotherapy exercises and occupational medical assistance, and 4) usual care. Intervention manuals allow individual tailoring. Primary outcome measures include Oxford Shoulder Score and sickness absence due to symptoms from the operated shoulder. Randomisation is computerised with allocation concealment by randomly permuted block sizes. Statistical analyses will primarily be performed according to the intention-to-treat principle.

**Discussion:**

The paper presents the rationale, design, methods, and operational aspects of the Shoulder Intervention Project (SIP). SIP evaluates a new rehabilitation approach, where physiotherapy and occupational interventions are provided in continuity of surgical episodes of care. If successful, the project may serve as a model for rehabilitation of surgical shoulder patients.

**Trial registration:**

Current Controlled Trials ISRCTN55768749.

## Background

Subacromial impingement syndrome (SIS) is an important cause of ill-health with a prevalence of 2-8% of the working population [1,2]. When non-surgical treatment fails, surgery may be chosen [3,4], and most often subacromial decompression is performed. Substantial increases in rates of surgical treatment of SIS have been reported from Sweden [5], the US [6], the UK [7], and Denmark [8]. In Denmark, a level of 0.15% of the working age population was reached in 2008. Although high proportions with successful outcomes have been reported, around 20% of the patients experience chronic shoulder pain and/or disability after surgery [9,10]. In Denmark, 10% of employed patients leave the labour market within two years after surgery due to health related disability [8].

Considering the fact that exercise therapy is widely used to help restore shoulder function after surgery ([name] et al., submitted, [11,12]), few randomised controlled trials (RCTs) have compared effects of different postoperative exercise programmes [13-16]. For musculoskeletal disorders, current evidence indicates that workplace-oriented interventions may be effective to promote work retention [17,18]. The majority of studies have focussed on low back pain [17,18], but different disease-specific risk profiles indicate that low back pain and upper extremity disorders may need different interventions [19]. Although work disability may lead to a poorer quality of life and loss of social identity [20], usual care of surgical shoulder patients does not focus on job retention as an important outcome, and to our knowledge, workplace-oriented interventions to promote work retention after subacromial decompression for SIS have not been evaluated.

The hypotheses of the Shoulder Intervention Project (SIP) are that postoperative physiotherapy exercises are more effective than usual care in improving shoulder function and that postoperative occupational medical assistance is more effective than usual care in promoting work retention.

## Methods/Design

### Design and setting

The study is a mainly pragmatic multicentre RCT [21]. The RCT is embedded in a cohort study, which comprises all patients aged ≥18–≤63 years who are referred to one of six public departments of orthopaedic surgery in Central Denmark Region on suspicion of SIS in a three year period, 2011–2014. Figure 1 presents the inclusion of patients and the stages of the RCT. The physiotherapy intervention will be evaluated for patients with and without paid work. The occupational intervention (and the physiotherapy intervention) will be evaluated for the subgroup of patients, who have paid work for at least 25 hours per week, using a factorial design [22,23]. Table 1 presents variables in the RCT and in the cohort study, in which the RCT is embedded.

**Figure 1 F1:**
[figure not shown]
**Flow chart following patients from inclusion into the cohort study through each stage of the randomised controlled trial to final data collection.** ^1^The Danish version of the Nordic Medico-Statistical Committee (NOMESCO) Classification of Surgical Procedures; ^2^Only patients in paid work for ≥25 hours per week; ^3^T_0_ = baseline; ^4^T_0_ = first contact to a department of orthopaedic surgery after inclusion into the cohort study.

**Table 1 T1:** Overview of variables in the randomised controlled trial (RCT) and in the cohort study, in which it is embedded

**Variable**	**Time of data collection and population**						
	**First orthopaedic contact**	**Shortly before surgery**	**Baseline**	**3 months**	**12 months**	**16 months**	**24/28 months**
	**Cohort**	**Cohort**	**RCT**	**RCT**	**RCT**	**Cohort§**	**RCT/Cohort§**
**Questionnaire**							
Job title	x	x	x	x	x	x	
Psychosocial working environment			x				
Work ability	x	x	x	x	x	x	
Work productivity and activity impairment				x	x		
Work modifications				x			
Advice to stop working				x			
Job centre initiated workplace visits				x			
Compensation claims	x		x				
Oxford Shoulder Score	x	x	x	x	x	x	
Shoulder pain intensity			x	x	x		
Duration of shoulder symptoms	x	x					
Global impression of change			x (since shortly before surgery)	x (since baseline)	x (since assessment at 3 months)		
Other musculoskeletal complaints		x	x		x		
EQ-5D-3L*	x	x	x	x	x	x	
Use of analgesics		x	x	x	x		
Non-surgical treatment		x (previous 3 months)	x (since operation)	x (previous 3 months)	x (previous 3 months)	x (previous 3 months)	
Expectations to surgery		x			x (fulfilment)		
Patient preferences			x				
Height, weight, handedness		x					
Smoking		x					
Physical activity		x	x	x	x		
Fear avoidance beliefs			x	x	x		
Self efficacy			x				
Mental health		x	x	x	x		
Satisfaction with SIP*				x			
Shoulder-related sickness absence				x			
Full return to own or other work with equal earnings					x	x	
**Shoulder examination and physical testing**							
Constant Score			x	x			
Range of motions			x	x			
Jobe’s test			x	x			
Painful arc test			x	x			
Hawkins’ test			x	x			
Scapular dyskinesis			x	x			
Maximum oxygen uptake			x	x			
Height, weight			x	x			
**Register data**							
Number of weeks receiving health-related transfer incomes					x	x	x

^§^At 16 and 28 months after first contact to a department of orthopaedic surgery, data is collected for the cohort except for patients in the RCT, for whom corresponding and more detailed data is collected at 12 and 24 months after RCT baseline. *Abbreviations are explained at the end of the paper.Regarding follow up occasions, please refer to Figure 1.

### Participants

To be included in the RCT, patients must have surgery under a main diagnosis of SIS or acromioclavicular osteoarthritis (International Classification of Diseases 10^th^ revision: M75.1-M75.8 or M19) and with a main shoulder surgery code of arthroscopic subacromial decompression (KNBH51, KNBH91, KNBG09, KNBL39, or KNBM79 according to the Danish version of the Nordic Medico-Statistical Committee Classification of Surgical Procedures). Exclusion criteria are shown in Figure 1. At postoperative clinical control after 8–12 weeks, eligible patients are provided with information material on SIP and are asked to participate in a brief telephone interview. Patients are only recruited if they have at least slight shoulder problems doing usual activities (e.g. work, study, housework, family or leisure activities) when assessed on a five level scale (no problems, slight problems, moderate problems, severe problems, unable). Furthermore, the patients’ employment status is assessed. Patients can be randomised to one of all four arms of the RCT if they are in paid work for at least 25 hours per week. Remaining patients can only be randomised to one of the two arms, which do not include occupational medical assistance. To be included, patients must also consent for acquisition of medical records. Figure 1 presents the inclusion procedure, which has been effective since April 2012, when it was changed due to slow recruitment. Until then, patients were excluded in case of previous shoulder surgery and/or diabetes, if they were not in paid work for at least 25 hours per week, and if they were not fulltime sick-listed.

Participation in SIP is based on the principles of informed consent. Participants are covered by the Danish patient insurance system. SIP provides compensation for documented loss of earnings and transportation costs. The study has been approved by the Central Denmark Region Committees on Biomedical Research Ethics (identification number: M-20100131) and by the Danish Data Protection Agency (journal number: 2010-41-4316).

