### Primary outcome measures

To evaluate the physiotherapy intervention at three months, the primary outcome measure will be change in shoulder function since baseline assessed by *Oxford Shoulder Score* (OSS), which ranges from 0 to 48 with 48 being the best outcome [29]. To evaluate the occupational intervention at three months, the primary outcome measure will be the *sickness absence percentage*, i.e. the number of hours of sick-leave due to symptoms from the operated shoulder in relation to the number of planned working hours within three months from baseline. This information is gathered by one month day-by-day calendars. Any hours off work to participate in the project will count in the outcome measure.

To evaluate the physiotherapy intervention at 12 months, the primary outcome measure will be *OSS.* For the subgroup, who are in paid work for at least 25 hours per week, the occupational intervention will be evaluated at 12 and 24 months, and the physiotherapy intervention will be evaluated at 24 months, using the primary outcome measure *transfer income percentage*, i.e. the number of weeks receiving temporary or permanent health-related transfer incomes within 12 and 13–24 months from baseline, respectively, divided by 52 weeks, according to the Danish National Register on Public Transfer Payments [30].

As a consequence of the change of inclusion criteria, we had to change the intended primary outcome measures for the occupational intervention at 3 and 12 months. The original measures at these follow up occasions were duration of fulltime sick-leave and duration of sick-leave until lasting return to work, respectively.

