### Statistical analyses

Trial results will be reported as a summary of the outcome measures in each group together with the estimated effect size and its precision. Statistical analyses will be performed according to the intention-to-treat principle, which will be supplemented by per protocol analyses depending on the proportion who do not receive the intended treatment. For outcomes measured using an essentially continuous scale (e.g. *OSS, sickness absence percentage,* and *transfer income percentage*), differences between groups at follow up will be compared by means of linear regression modelling with appropriate transformation of dependent variables. Analyses of effects of the physiotherapy intervention will be adjusted for centre (department of occupational medicine), for the occupational intervention (no, yes, irrelevant), and for the outcome measure at baseline. For the subgroup, who are in paid work for at least 25 hours per week, a two-by-two factorial design will be used. The analyses will focus on main effects of the occupational intervention, but cell-by-cell results will also be reported [22,23]; the analyses will be adjusted for centre. Numbers needed to treat for one patient to benefit from the interventions will be calculated [37]. In addition to main RCT results, supplementary analyses will be performed using variables presented in Table 1.

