### Sample size calculations

The calculations are based on the primary outcomes *OSS, sickness absence percentage, and transfer income percentage.* With 65 participants, who receive physiotherapy exercises, and 65 participants, who do not, a difference in mean *OSS* of 2.4 points can be detected at 12 months with power = 0.8, alpha = 0.05, an assumed standard deviation of 9.0 *OSS* points, a correlation between *OSS* at baseline and follow up of 0.5, and 10% dropout (we expect less than 10% dropout at three months). With 50 participants, who receive occupational medical assistance, and 50 who do not, a difference in mean *sickness absence percentage* of 11.9% can be detected with power = 0.8, alpha = 0.05, an assumed standard deviation of 20%, and up to 10% dropout at three months; the same power is expected for the *transfer income percentage* after 12 and 13–24 months since these outcome measures are based on register information with practically complete follow-up. Power calculations were carried out with STATA 13 software (StataCorp LP, College Station, TX, USA; power pairedmeans and twomeans, respectively).

According to analyses of data from the Danish National Patient Register and the Danish National Register on Public Transfer Payments, around 1150 patients had an arthroscopic subacromial decompression for SIS in Central Region Denmark in 2008, and 67% of these patients had surgery at public hospitals. Thus, we find it realistic to recruit 130 patients within the inclusion period. Originally, we intended to include 400 patients, but with the change of inclusion criteria and outcome measures for the occupational intervention, the necessary sample size was reduced.

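### The occupational analysis is adjusted for centre only, although patients randomised before April 2012 all had to be full-time sick-listed and later ones did not; an eligibility-period term would recover some precision

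*Protocol article*

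**What the plan says.** **Eligibility.** The Participants section describes an inclusion procedure "which has been effective since April 2012, when it was changed due to slow recruitment". Before that date patients were excluded "if they were not in paid work for at least 25 hours per week, and if they were not fulltime sick-listed", and also for diabetes or earlier shoulder surgery. Now anyone meeting the working-hours condition can be randomised to all four arms, whether sick-listed or at work.

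**Outcomes.** The Primary outcome measures section reports that "we had to change the intended primary outcome measures for the occupational intervention at 3 and 12 months". The original measures "were duration of fulltime sick-leave and duration of sick-leave until lasting return to work, respectively". The new 3-month measure is hours of shoulder-related sick leave as a percentage of planned hours, taken from day-by-day calendars. The new 12-month measure is the percentage of weeks on health-related transfer income, taken from a national register.

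**Analysis.** The Statistical analyses section specifies linear regression. For the two-by-two factorial part, which carries the occupational comparison, it says that "the analyses will be adjusted for centre". The physiotherapy analyses are adjusted for centre, for the occupational intervention and for the baseline value of the outcome. Randomisation is stratified by surgical department, not by period or sick-listing.

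**Sample size.** With 50 against 50 patients, "an assumed standard deviation of 20" per cent, power 0.8, alpha 0.05 and up to 10% dropout, the detectable difference in mean sickness absence percentage is given as 11.9.

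**The concern.** The working subgroup appears to come from two eligibility regimes that differ on the very construct the 3-month outcome measures. A patient fully off work at entry can be expected to lose a larger share of planned hours over the next three months than one already working. If so, regime is a strong prognostic factor that is known for everyone at randomisation. A model with treatment factors and centre leaves that variation in the residual. The confidence interval for the occupational effect is then wider than it need be, in a comparison planned at 80% power under the assumed dropout. The 12- and 24-month transfer-income outcomes could be affected in the same way.

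This is not detail left to another document. The article states a covariate set for this comparison, and it is thinner than the set stated for physiotherapy.

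**Working it through.** **Step 1: reproduce the stated figure.** Inputs from Sample size calculations: 50 per group, 10% dropout (45 analysed), SD 20, power 0.8, alpha 0.05 (two-sided assumed).

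- Normal approximation: 20 × (1.960 + 0.842) × √(2/45) = 11.81.
- t-based: 11.94, which is about 0.597 × SD. Power at 11.9 is 0.797.

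The stated 11.9 is confirmed.

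**Step 2: what a period term removes.** Let f be the share randomised before April 2012 and D the difference in mean sickness absence percentage between periods. Neither is in the article, so both are assumed. Period then accounts for f(1 − f)D² of the variance. Taking SD 20 as that of the whole analysed sample (variance 400), the residual SD after adjustment is √(400 − f(1 − f)D²). The detectable difference is about 0.597 times that, ignoring the lost degree of freedom.

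| f | D | f(1 − f)D² | Share of variance | Residual SD | Detectable difference | Power at 11.9 |
|---|---|---|---|---|---|---|
| – | 0 | 0 | 0% | 20.00 | 11.94 | 0.797 |
| 0.05 | 10 | 4.75 | 1.2% | 19.88 | 11.87 | 0.802 |
| 0.05 | 30 | 42.75 | 10.7% | 18.90 | 11.29 | 0.840 |
| 0.10 | 20 | 36 | 9.0% | 19.08 | 11.39 | 0.833 |
| 0.10 | 30 | 81 | 20.3% | 17.86 | 10.67 | 0.878 |
| 0.20 | 20 | 64 | 16.0% | 18.33 | 10.95 | 0.861 |
| 0.20 | 30 | 144 | 36.0% | 16.00 | 9.55 | 0.937 |

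**Step 3: bias and error rate.** The comparison was simulated with 90 patients in two arms, sequential blocks of 4, 8 and 12, f from 0.10 to 0.30, D of 20 or 30, and 4,000 runs per setting.

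- The unadjusted estimate was unbiased: about 0 under no effect and about 11.9 when the true effect was 11.9.
- Under no effect the unadjusted test rejected in 1.2–4.2% of runs, and the adjusted test in 4.9–5.2%.
- At a true effect of 11.9, power rose from 0.797 to 0.830 (f = 0.10, D = 20) and from 0.847 to 0.937 (f = 0.20, D = 30).

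Blocking already balances the arms over time to a large extent, so the loss appears as a standard error that is too large. The last case also shows that Step 2 can overstate the gain: it starts from 0.797, whereas the blocked simulation starts from 0.847.

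**Limits.** All of this is on the raw scale, while the article allows transformation of the outcome. The simulation did not use separate strata by surgical department.

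**The case against.** **The size is unknown and may be nil.** This stands. At f = 0.05 and D = 10, power moves only from 0.797 to 0.802. Slow recruitment suggests that the early share may be small. That early patients exist and are pooled is implied by the 2011–2014 inclusion period and the April 2012 change; it is not stated.

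**Covariates can be left to an analysis plan.** This stands for covariates a protocol does not mention. Here the adjustment is stated, so naming a better one is a comment on what is written.

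**Period is only a proxy.** This also stands. Patients entering after April 2012 may be full-time sick-listed too. Sick-listing at baseline is the more direct covariate, but Table 1 lists no such item; shoulder-related sickness absence appears there at 3 months only. Period is known for everyone from the randomisation date.

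**Stronger readings that the article does not support.** A reader might infer that the stated power is wrong. If 20 were the SD within one period, the pooled SD at f = 0.20 and D = 30 would be √(400 + 144) = 23.3, and power at 11.9 would be 0.668. But the article links the reduced sample size to the new criteria and outcomes, so 20 reads more naturally as the SD of the sample to be analysed. Nor is 80% a ceiling, since it already assumes the largest expected dropout.

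A reader might also suspect the outcome change in an unblinded trial. The article discloses it, names the original measures and ties it to eligibility. Duration of full-time sick leave is zero or undefined in a patient who is not sick-listed. OSS and the 24-month outcome are not among the changed measures, and the new 12-month measure is register-based.

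**Conclusion.** The point holds as a matter of efficiency. A prognostic split that the eligibility history makes plain, and that is known at randomisation, is left out of the stated occupational model. Validity is not in question: the estimate is unbiased and, in the settings simulated, the unadjusted test errs towards caution.

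The gain from adjustment cannot be derived from the article. Assuming f of 5–20%, D of 10–30 points and a pooled SD of 20, the detectable difference goes from 11.9 to somewhere between about 11.9 and 9.6. In none of the settings tried did the term reduce power. The article does not show that the sample-size statement is wrong or that the outcome change was driven by results.

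**What to change.** 1. Add an indicator for randomised before / from April 2012 to the occupational models for the 3-, 12- and 24-month outcomes.
2. Add full-time sick-listing at baseline where it can be derived, for example from the transfer-payment register or from the employment status asked about in the recruitment interview. Use only information dated up to randomisation; calendar entries made after it are not baseline data.
3. Report how many patients were randomised before April 2012.
4. Optionally, as a sensitivity analysis, report the two original outcomes in patients full-time sick-listed at baseline, if the calendars and register allow it. This would need a definition of lasting return to work, which the article does not give.

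The first two items cost one or two degrees of freedom and a sentence in the analysis section. Item 2 also needs a check that the source records status at the baseline date. According to Trial status, the working subgroup was still being recruited and only the 3-month physiotherapy analysis was under way, so the occupational model could still be fixed in advance.

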### Interventions

#### Occupational medical assistance

After randomisation, the patient is seen by an occupational physician from the research team, who assesses the patient’s work instability using a gold standard approach [24]. Work instability is characterised by a mismatch between an individual’s functional capabilities (in this case shoulder function) and job demands (in this case biomechanical shoulder load) to an extent where job retention is threatened [24]. Shoulder function is assessed by clinical examination and shoulder load is assessed using a job exposure matrix (JEM), both combined with a semi-structured interview. Depending on the degree of work instability, a three month action plan is constructed. The plan is attuned to the patient’s most important barriers against continuing or resuming work, in agreement with the biopsychosocial model [25,26].

A JEM based on expert ratings is used [27]. The JEM comprises shoulder force requirements using a 5-point force score scale, postural load in terms of daily duration of work with the arm elevated >90°, daily duration of moderately repetitive work with ≥4-<15 upper arm movements per minute, and highly repetitive work with ≥15 upper arm movements per minute. Jobs are classified as having *high shoulder load* (indicated by a red colour code) if they fulfil at least one of the following criteria: a force-score ≥3, upper arm elevation >90° ≥1 hour/day, highly repetitive work ≥½ hour/day, and moderately repetitive work ≥4 hours/day. Remaining jobs are classified as having *medium shoulder load* (indicated by a yellow colour code) in case of highly repetitive work <½ hour/day and at least one of the following: a force-score >1.5-<3, upper arm elevation >90° ≥½-<1 hour/day, and moderately repetitive work ≥2-<4 hours/day. Those jobs, which fulfil all of the following criteria, are classified as having *low shoulder load* (indicated by a green colour code): a force-score ≤1.5, upper arm elevation >90° <½ hour/day, highly repetitive work <½ hour/day, and moderately repetitive work <2 hours/day. In the semi-structured interview, the physician gets a description of the patient’s primary work tasks in order to individualise the JEM-based exposure assessment and to identify work tasks with relatively high shoulder load. The interview also covers shoulder symptoms, general health status, and the patient’s assessment of the most important barriers against continuing or resuming work. The physician interprets and scores the patient’s 1) shoulder function, 2) shoulder load, 3) worries that the work may harm the shoulder, even though the job entails low shoulder load, 4) influence on the way work tasks are performed and on task distribution, and 5) support from employer/supervisor or colleagues with respect to work modifications. Each of these five items is scored on an 11-point numeric rating scale ranging from 0 (no problem) to 10 (the largest possible problem).

Table 2 presents our algorithm to assess work instability, indications for workplace visits, and intervention levels. An indicated workplace visit may be omitted if the patient can arrange workplace adaptations him-/herself, or if the employer is against a visit. In some cases, it may suffice that the physician contacts the workplace by telephone. Workplace visits are performed within 10 working days, attended by the occupational physician, the patient, and the employer/supervisor. The duration is around one hour. The physician assesses the patient’s shoulder load by observation. Tasks with relatively high shoulder load are identified, and potential solutions are discussed in order to reach an agreement on work adaptations that are feasible within a short time horizon, i.e. adaptations characterised by low costs, low complexity, and compatibility with existing work structures. Deadlines are set for implementation of the adaptations and their duration is stipulated. Advice on far-reaching, long-term adaptations may be passed on. The physician classifies the planned workplace adaptations as technical solutions, reductions of working hours (part-time sick-listing), or modifications of task distribution [28]. The plan may represent more than one of these categories. To enable coordination of workplace-oriented efforts, the physician may contact the patient’s municipal job centre.

**Table 2 T2:** **Algorithm to assess work instability, indications for workplace visits, and intervention levels, modified from **[24]

**Level of work instability**	**Specification of work instability**	**Indication for workplace visit and level of intervention**
Level 0	Shoulder function is adequate to perform all work activities, pain is under control, work activities do not imply a risk to the shoulder (job colour code: green), and the patient does not worry that this is the case.	No
Level 1	As above, but from time to time pain is a problem, work activities do not imply a risk to the shoulder (job colour code: green), but the patient worries that this may be the case, and/or the patient experiences that the employer hesitates to let the patient do his or her ordinary work activities in order to protect the shoulder.	Maybe – the indication is relative. Reassure the patient (and the employer) that work can be continued/resumed.
Level 2	Work activities do not imply a risk to the shoulder (job colour code: green), but pain is aggravated to an unacceptable level, and/or shoulder function does not match all work activities. The shoulder problems are expected to resolve within 6–12 months.	Yes, temporary solutions have to be established at the workplace.
Level 3	Some work activities imply a risk of worsening the shoulder condition (job colour code: yellow or red), pain is aggravated to an unacceptable level, and/or shoulder function does not match all work activities. The shoulder problems are not expected to resolve within 6–12 months.	Yes, permanent solutions have to be established at the workplace.
Level 4	Major work activities imply a risk of worsening the shoulder condition (job colour code: yellow or red), pain is aggravated to an unacceptable level, and/or shoulder function does not match the work demands. The shoulder problems are not expected to resolve within twelve months.	Yes, a permanent shift to another job may be necessary.
Undetermined	A workplace visit is necessary to assess work instability.	Yes, shoulder load has to be assessed.

Job colour codes (middle column) are based on a job exposure matrix combined with a semi-structured interview.

The patient receives a note with the agreed plan, advice on general physical activity, and transference of questions concerning analgesics to the patient’s general practitioner. If warranted, the physician notifies the shoulder disorder as a possible industrial injury in accordance with Danish legislation.

After six weeks, the physician contacts the patient by telephone to assess adherence to the plan. If needed, the employer/supervisor is contacted. Three months after baseline, the patient is seen for final evaluation and workplace-oriented advice. The patient’s assessment of factors facilitating or hindering the plan is registered, and any adverse events are noted. The intervention is described in a detailed manual.

